**Metadata questionnaire**									
	Total number of questions, n	46		56		65		88	
	Minutes to complete	10 -20		15-20		15-20		25-30	
**Conceptual model explaining health effects**									
	Eating behavior	✓		✓		✓		✓	
	Loneliness	✓		✓		✓		✓	
	Autonomy, competence, and relatedness	✓		✓		✓		✓	
	Quality of life	✓		✓		✓		✓	
**Conceptual model explaining ECA^a^ use**									
	Relationship with ECA^a^			✓		✓		✓	
	Usability							✓	
	Enjoyment							✓	
	Aesthetics							✓	
	Privacy concerns							✓	
	Control							✓	
	Perceived usefulness							✓	
**Other constructs**									
	User experience					✓			
	Willingness to pay							✓	

^a^ECA: embodied conversational agent.

After 4 weeks of use, participants will receive an email with an invitation to complete the online T1 questionnaire, assessing all their health factors, their relationship with the ECA, and their user experience. After 8 weeks of use, participants will receive an email with an invitation to complete the T2 questionnaire, assessing all their health and use factors and willingness to pay. In addition, participants will be asked whether they are open to an interview lasting half an hour, in which the researcher will ask about their user experience.

At all stages of the study, participants will be able to contact the researchers by email or phone for any questions or problems. In the PACO app, there is a contact form. Depending on the participant’s problem and preference, one of the researchers will email, phone, or visit the participant. If a participant has not interacted with PACO for 7 days, the participant will also be contacted and asked whether there are any problems.

### Intervention

#### PACO App

PACO is a fully automated web-based eHealth app in which 2 ECAs engage in dialogue with older adults in order to motivate them to change their dietary behavior and decrease their loneliness (Figure 4 and Multimedia Appendix 2). The app consists of 5 modules, each one applying different BCTs (Table 2). During the onboarding process, the ECAs introduce themselves and explain the PACO program. There is a daily dialogue between either Herman (the cook, who provides nutritional advice) or Ellen (the peer, who provides social advice) and the user. Users are asked to use the food diary module for the first 7 days in order to increase their awareness of their eating behavior. All other modules become available when the food diary has been completed for 7 days or automatically after 14 days. During and after the 8-week program, the ECAs encourage users to continue the health behavior changes that they have implemented during the intervention in their daily lives.

**Figure 4 figure4:**
[figure not shown]
PACO app home screen.

**Table 2 table2:** The modules of the PACO app.

Week	Module	Behavior change technique	SDT^a^ component, target behavior	Rationale
1	Food diary	Self-monitoring	Autonomy, eating behavior	Users record what they have eaten, with whom, and how they appreciated the meal. There is an option to set reminders. When users know what they eat and drink, we aim to give them the feeling that they are able to change their behavior [37], leading to an actual change in eating behavior.
2-8	Goals	Action planning	Competence, eating behavior and loneliness	Users can choose from a list of social and eating goals. Via dialogue, Ellen explains the goal and provides tips. Users create a personal action plan and track their progress, with the option to set reminders. When users carry out their plans, we aim to improve their feelings of competence [31], leading to changes in eating behavior and feelings of loneliness.
1-8	Recipes	Tailoring and self-efficacy	Autonomy, eating behavior	Via dialogue, Herman helps users select a healthy and easy-to-prepare recipe (>280), based on users’ dietary wishes and preferences. By assisting users in cooking their own meals in line with their preferences, we hope to increase feelings of autonomy via self-efficacy [38], leading to a change in eating behavior.
1-8	Stories	Social learning	Relatedness, loneliness	Users can listen to stories from other older adults about physical or virtual social activities they perform. Ellen can provide more information on the activity. When users learn from each other, we hope that they will feel more related to others and have fewer feelings of loneliness [39,40].
1-8	Chat	Social facilitation (peer support)	Relatedness, loneliness	Via WhatsApp groups, users can interact with one another. Ellen is also included and asks questions. When users interact with one another, we hope that they will experience increased feelings of relatedness and decreased feelings of loneliness [41,42].

^a^SDT: Self-determination Theory.

#### Development of the Intervention

The PACO development process was based on the first 3 steps of the Center for eHealth Research and Disease Management (CeHRes) Roadmap [43]: the contextual inquiry, the value specification, and the design phase. The contextual inquiry phase consisted of 3 parts. First, the current practices in designing and evaluating ECAs for coaching people in the health context were identified via a scoping review [12]. Second, factors contributing to healthy living and healthy and unhealthy eating among Dutch community-dwelling older adults were identified via a 7-day diary and via multiple focus groups [44]. Third, an initial stakeholder analysis was carried out, and key stakeholders were identified [45].

During the value specification phase, healthy eating tips were explored via 2 additional focus group sessions [44]. The preferred approach, source, and tone of voice for healthy eating tips were discussed. In addition to the focus group, interviews were held with key stakeholders in order to identify their requirements [45].

The design phase of the PACO app was based on the previous 2 phases. In addition, the SDT [29] was used as a foundation. Self-monitoring, action planning, tailoring, self-efficacy, social learning, and social facilitation were selected as BCTs. In the design phase, first, 3 ECAs were created, each with a different role. In order to ascertain their persuasiveness, an online experiment using various mockups was carried out. Via a focus group, the findings were discussed, and the layout of the 2 preferred ECAs was improved. All input was used to create a first version of the app, which was tested via a usability study [46]. All usability issues were resolved, leading to the final app.

### Data Collection

The main study parameters include use, eating behavior, and loneliness. Use will be assessed via data logs, which will be collected by the PACO app. More specifically, data logs contain the user ID, timestamp, dialogue, and ECA (either Ellen or Herman). In addition, data logs contain the number of goals achieved, the diary input, and the chat history. Eating behavior will be self-assessed by 3 open questions, based on a 24-hour recall format. The questions include the following: (1) Did you eat fruit yesterday? If so, what kinds of fruit, what time, and how many grams per piece? (2) Did you eat vegetables yesterday? If so, what kinds of vegetables, what time, and how many grams per piece? (3) Did you drink yesterday? If so, what kinds of drink, what time, and how many glasses, cups, or milliliters? Loneliness will be self-assessed via a questionnaire (Table 3).

**Table 3 table3:** Details of the questionnaires.

Factor	Questionnaire	Items, n	Scale	Modifications
Loneliness	De Jong Gierveld Loneliness Scale [47]	6	1-5	None
Autonomy, competence, and relatedness	Basic Psychological Need Satisfaction and Frustration Scales [48-50]	24	1-5	None
QoL^a^	Brief Older People’s Quality of Life [51]	13	1-5	Translated to Dutch
Relationship with ECA^b^	Rapport Scale [52-54]	10	1-5	Translated to Dutch; ‘virtual coach’ instead of ‘coordinator’
Usability	System Usability Scale [55]	10	1-5	Translated to Dutch
Enjoyment	Affect Scale [56]	4	1-5	Translated to Dutch
Aesthetics	Classic Aesthetics [21]	5	1-7	Translated to Dutch
Privacy concerns	Concern for Privacy Scale [24]	4	1-7	Translated to Dutch
Control	Active Control [57]	4	1-7	Translated to Dutch; ‘PACO’ instead of ‘website’
Perceived usefulness	Perceived Usefulness Scale [28,58]	3	1-5	Translated to Dutch; ‘PACO’ instead of ‘the robot’

^a^QoL: quality of life.

^b^ECA: embodied conversational agent.

The secondary study parameters include self-determination (autonomy, competence, relatedness), QoL, relationship with ECA, usability, enjoyment, aesthetics, privacy concerns, control, and perceived usefulness. All these parameters will be measured via validated, self-assessed, online questionnaires.

In addition, 2 other parameters include willingness to pay and user experience. Both parameters will be assessed via self-compiled questionnaires. Participants will be asked whether they are willing to pay for PACO (*yes*/*no*) and the amount they are willing to pay for PACO for 3 months [€0, €5 (USD $6.09), €10 (USD $12.18), or €20 (USD $24.35) per month]. Via a questionnaire, participants will be asked 9 open-ended questions about their user experience in general (eg, How did you experience using PACO the last 4 weeks?) and per module (eg, Which modules did you perceive as useful, and why?). In addition, participants will be asked why they kept using PACO, why they stopped using PACO, and whether they wish to share something else. Via an interview of approximately 30 minutes, participants will be asked about their general experience, the modules, how and where they used PACO, experienced behavior change, and the two coaches. Via these questions, we aim to gain a more fine-grained understanding of users’ experiences and triangulate our quantitative results.

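### The printed fruit and vegetable recall questions ask for grams per piece but not the number of pieces or total amount, so intake cannot be derived uniformly for a primary outcome

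*Protocol article*

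**What the plan says.** The Data Collection section names the primary parameters: "The main study parameters include use, eating behavior, and loneliness". The abstract also lists eating behavior among the primary outcomes. The instrument is described as follows: "Eating behavior will be self-assessed by 3 open questions, based on a 24-hour recall format".

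The three questions are printed. For fruit: "Did you eat fruit yesterday? If so, what kinds of fruit, what time, and how many grams per piece". For vegetables: "Did you eat vegetables yesterday? If so, what kinds of vegetables, what time, and how many grams per piece". For drinks, the respondent is asked "what kinds of drink, what time, and how many glasses, cups, or milliliters".

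Table 1 places eating behavior in the control, T0, T1 and T2 questionnaires. The Data Analysis section compares these time points with within-subject t tests and tests the two conceptual models by PLS-SEM. Eating behavior belongs to the health-effects model.

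**The concern.** A daily amount of fruit or vegetables is a count multiplied by a unit size. The printed questions ask for the unit size and leave out the count. The drink question asks for a quantity, and asking for grams has little purpose unless an amount is wanted, so the omission looks unintended. For chopped or cooked vegetables, grams per piece has no clear meaning at all.

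Both planned analyses need a number for eating behavior. If some answers allow an amount to be worked out and others do not, the gap has to be filled by inference, and the inference differs by respondent. It may also differ by wave within a respondent, and that matters most for a paired comparison. An analysis plan cannot recover an amount that the questionnaire never requested.

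**Working it through.** **Step 1. What each question requests.**

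| Question | Kind | Time | Unit size | Count or total |
|---|---|---|---|---|
| Fruit | yes | yes | grams per piece | not asked |
| Vegetables | yes | yes | grams per piece | not asked |
| Drinks | yes | yes | glass, cup or milliliter | asked |

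**Step 2. Could a separate count question exist that the article does not print?** Table 1 gives "Total number of questions, n 46 56 65 88" for control, T0, T1 and T2. The inputs come from Table 3 and the Data Collection text:

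- eating behavior 3
- loneliness 6 ("De Jong Gierveld Loneliness Scale [47] 6")
- autonomy, competence and relatedness 24 ("Basic Psychological Need Satisfaction and Frustration Scales [48-50] 24")
- quality of life 13
- relationship with the agent 10
- user experience 9
- use-model scales 10 + 4 + 5 + 4 + 4 + 3 = 30
- willingness to pay 2 (whether, and how much)

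The sums are:

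- Control: 3 + 6 + 24 + 13 = 46
- T0: 46 + 10 = 56
- T1: 56 + 9 = 65
- T2: 56 + 30 + 2 = 88

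All four stated totals are reproduced exactly with eating behavior counted as three questions. Two separate count questions would have made the control questionnaire 46 + 2 = 48. There is no room for an unlisted one.

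**Step 3. Could another source supply the count?** Table 2 describes the food diary as recording what was eaten, the company and how the meal was liked, with no mention of amount. It is an app module scheduled for week 1, so it does not exist when the control questionnaire is completed and is not scheduled for T1 or T2.

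**Step 4. Size of the ambiguity.** Amount per day = number of pieces × grams per piece. Take 100 g per piece (an assumed weight; the article gives none). The same answer fits 1 × 100 = 100 g, 2 × 100 = 200 g or 3 × 100 = 300 g. The amount is undetermined by a factor equal to the unreported count.

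**Step 5. Effect on a paired comparison (illustration, same assumed weight).** Suppose a person eats two pieces at both T0 and T1, gives no count at T0 and volunteers one at T1. If an answer without a count is read as one piece (also assumed), the recorded change is 200 − 100 = +100 g, although nothing changed.

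**The case against.** The strongest reply is that these are open questions in recall format. A respondent can list each piece with its time, or volunteer a count, so some totals will be recoverable. That stands. A reader might infer that fruit and vegetable intake cannot be calculated at all; the article does not support that. The defect is that the amount is not obtained uniformly.

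Second, the article never defines eating behavior as total grams per day. Whether fruit or vegetables were eaten, the number of kinds and perhaps the number of occasions can still be derived. That also stands, and the scoring rule may sit in the full protocol or analysis plan, so its absence here is no fault. But a scoring rule based on amount would need data that these questions do not request.

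Third, the study runs in Dutch and the article prints English. The fielded questions may differ from the printed ones. This cannot be checked from the article and is a real limit on the point.

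A reader might also go on to criticise the single recall day as mixing weekdays and weekends, or attach a figure for lost effect size. The documents do not support either. T1 and T2 follow at 4 and 8 weeks of use, whole numbers of weeks, so invitations by default fall on the same weekday, although late completion can shift this. No day-to-day variance is given, so any attenuation figure would rest on an assumed ratio. A single recall day is a disclosed choice in a study that calls itself explorative. Nor does a missing count justify redefining the primary eating variable or demoting drinks.

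**Conclusion.** The point holds in limited form. As printed, two of the three questions for a primary outcome request unit weight without number or total, and nothing else described in the article fills the gap. Total fruit and vegetable intake cannot be derived reliably or uniformly across respondents and waves. The drink question is unaffected.

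For an answer without a count, the uncertainty is a factor of the number of pieces, for example threefold between one and three. How many answers will lack a count is unknown, so the loss in the t tests and the PLS-SEM cannot be quantified. The conclusion assumes that the printed wording matches the fielded questionnaire. It is a flaw in stated item wording and is worth correcting, but it does not invalidate the outcome.

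**What to change.** First check the fielded Dutch questions. If they already ask for number or total, correct the printed wording. If not, extend questions 1 and 2 to ask either for the number of pieces or portions and the size of each, or for the total amount eaten, so that a daily quantity can be computed. Portions or a total would also suit vegetables that do not come in pieces.

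Done inside the existing questions, this leaves the Table 1 totals at 46, 56, 65 and 88 and adds very little burden.

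The cost lies in the transition. The article reports that recruitment has begun, so some control or T0 answers may already exist under the present wording. Flag them by wording version. A within-person comparison that spans both wordings is not like for like, and flagging alone does not repair it. Repeat the affected t tests as a sensitivity analysis restricted to participants whose compared waves used the same wording, and report both results.

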### Data Analysis

Descriptive statistics will be used for participant demographics, data logs, and willingness-to-pay data. Data logs will be used to determine the frequency of login, time spent on each module, time spent in total, time of use, and time of dropout. If a participant has not interacted with PACO for 14 consecutive days, they will be treated as a dropout and omitted from further analysis. The within-subject *t* test will be used to compare effects between control, T0, T1, and T2. PLS-SEM will be used in 2 phases per model to test the conceptual models. In phase 1, the measurement model will be validated by testing the constructs separately to determine internal validity [using structural equation modeling (SEM)-oriented criteria and a traditional Cronbach alpha]. In addition, it will be determined whether there is multicollinearity. If there is an acceptable measurement model, phase 2 will be carried out. The causal model will be tested and, if necessary, optimized. A conservative approach will be adopted whereby the theoretical model will be adjusted only if this results in a large improvement in the model. The quality of the causal model will be determined on the basis of PLS-SEM specific goodness-of-fit indices. All analyses will be performed in SPSS (version 24; IBM Corp) and SmartPLS (version 3; SmartPLS GmbH).

Audio recordings of the interviews will be transcribed until data saturation is reached. The transcripts of, and answers to, the open user-experience questions will be uploaded in ATLAS.ti qualitative data analysis software (version 8.4; ATLAS.ti Scientific Software Development GmbH). Analysis will be guided by a thematic analysis approach [59], combining a deductive and an inductive approach. The protocol for the focus group will be used to generate deductive codes. An initial list of inductive codes will be generated by LK and supplemented independently by another researcher. Differences will be discussed, leading to a final and agreed upon codebook. Each transcript will be coded by LK and another project member. Differences will be discussed again, leading to a final coded transcript.

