**Methods:**

The web-based eHealth app PACO is a fully automated 8-week intervention in which 2 ECAs engage older adults in dialogue to motivate them to change their dietary behavior and decrease their loneliness. PACO was developed via a human-centered and stakeholder-inclusive design approach and incorporates Self-determination Theory and various behavior change techniques. For this study, an unblinded randomized controlled trial will be performed. There will be 2 cohorts, with 30 participants per cohort. Participants in the first cohort will immediately receive the PACO app for 8 weeks, while participants in the second cohort receive the PACO app after a waiting-list condition of 4 weeks. Participants will be recruited via social media, an online panel, flyers, and advertorials. To be eligible, participants must be at least 65 years of age, must not be in paid employment, and must live alone independently at home. Primary outcomes will be self-assessed via online questionnaires at intake, control, after 4 weeks, and after 8 weeks, and will include eating behavior and loneliness. In addition, the primary outcome—use—will be measured via data logs. Secondary outcomes will be measured at the same junctures, via either validated, self-assessed, online questionnaires or an optional interview.

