### Conceptual Models

In order to conceptualize and measure engagement, Cole-Lewis et al [19] state that it is necessary for users to have appropriate levels of interaction with the technology and that the behavioral change components are relevant. Hence, we present 2 conceptual models. The first is a conceptual model explaining ECA use (CEU; Figure 1). With this model, we aim to explain the factors that determine the use of an ECA intervention in this context. The second is a conceptual model explaining health effects (CHE; Figure 2). With this model, we aim to explain the mechanisms behind the observed change in eating behavior and loneliness.

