**Figure 2 figure2:**
[figure not shown]
Conceptual model explaining health effects, known as CHE.

Use is at the center of the conceptual model explaining ECA use. It is assumed that an eHealth intervention will not be used if it does not create any benefit (perceived usefulness) or if it has a substantial number of usability problems [20]. Visual aesthetics, defined as an orderly and clear design, are closely related to many of the design rules advocated by usability experts [21]. In the case of patient portals, aesthetics have thus been found to influence usability in the context of explaining technology acceptance [22]. We expect perceived usefulness to be influenced by 3 user experience factors. Perceiving something as enjoyable is linked to a positive effect on use when the system is perceived to be useful [23]. Willingness to share personal information and preferences (ie, the absence of privacy concerns) is argued to be a prerequisite for convenience and a useful system [24]. The last factor is control, which refers to “the extent to which the user can bring about or prevent particular actions or states of the system if she has the goal of doing so” [25]. Especially in human-computer interaction literature, control has been identified as a crucial factor in the occurrence of perceived usefulness and use [26,27]. Furthermore, there is robust evidence that usability has a direct effect on perceived usefulness [28]. In turn, use is hypothesized to act as an antecedent of the intensity of an end user’s relationship with an ECA [14].

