### Ethical Considerations

The study has been approved by the medical ethical committee of Wageningen University (number NL73121.081.20) and has been registered at ClinicalTrials.gov before the enrolment of participants (identifier NCT04510883). As participants are not exposed to any risks, a data safety monitoring board will not be used during the study. Participants will invest time in this study; they have to complete multiple surveys and use the PACO app for 8 weeks. We believe that this duration and data collection are needed to gain a fine-grained understanding of the app’s use, relationship development, and the process of health behavior change. The main benefit to participants is that they gain insight into their health behavior via the PACO app. In addition, in prior studies, we found that participants highly appreciate the attention given to them via such studies.

Prior to the study, people will receive an information letter. They will have 2 weeks of consideration time and can contact the researcher (LK) or an independent expert with any questions. Participants can leave the study at any time for any reason if they wish to, without any consequences; participants will not be replaced.

All collected data will be kept in secure online databases that are password-protected, with access limited to the study team.

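### The 14-day inactivity rule removes participants from the effect tests and the CEU according to use, which is itself a primary outcome

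*Protocol article*

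**What the plan says.** The rule is in the Data Analysis section: "If a participant has not interacted with PACO for 14 consecutive days, they will be treated as a dropout and omitted from further analysis". The sentence before it lists what the logs will yield, including time of dropout. The sentences after it name the within-subject t test across control, T0, T1 and T2, and then PLS-SEM for both conceptual models. No analysis of all randomised participants is named.

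Use is an outcome in its own right. The abstract says that "the primary outcome—use—will be measured via data logs", and Data Collection states: "The main study parameters include use, eating behavior, and loneliness". The CEU has use at its centre, and its stated purpose is that "we aim to explain the factors that determine the use of an ECA intervention in this context". Research Questions also asks about use over time.

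Under Ethical Considerations, "participants will not be replaced". In Data Collection, the user-experience questions include "why they stopped using PACO".

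**The concern.** A person who stops interacting with PACO has produced a value of the use outcome: low or none. The rule treats that value as a reason to delete the person, and it acts after randomisation. Three things follow.

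- **Effect estimates.** The t tests on eating behaviour and loneliness describe only those who kept using the app. If people who persist also tend to improve more, the estimated change is too favourable.
- **The CEU.** The Conceptual Models section assumes that an eHealth intervention goes unused when it brings no benefit or has many usability problems. The participants most likely to show that mechanism are removed before the model is fitted. Restricting the range of use weakens the associations that the model is meant to detect.
- **Numbers.** The analysed sample falls below 60 and is not topped up.

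This is not a detail left to a fuller document. The article states the exclusion outright, and a later plan could only keep or reverse it.

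**Working it through.** **Inputs from the article.** Planned sample 60 (30 per cohort), based on the 10-times rule; the 14-day rule; no replacement. The article gives no dropout rate, no correlation between use and any other variable, and no effect size. The omission shares d and the correlations below are therefore assumptions, shown as ranges.

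**Step 1: the plan's own figure.** The 10-times rule gives N = 10 × the largest number of paths pointing at one construct. The path count is not in the text and the model figures are not shown. The Conceptual Models text names four influences on perceived usefulness (enjoyment, privacy concerns, control, usability), which gives 10 × 4 = 40. A target of 60 corresponds to six paths. The 60 can be neither confirmed nor faulted from the text, and the point does not depend on it.

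**Step 2: number analysed.** N(d) = 60 × (1 − d). The results are in the table. More than one third omitted would leave fewer than the 40 that the four visible paths require.

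**Step 3: range restriction in the CEU.** Take use and a predictor as bivariate normal with true correlation r, and remove the lowest share d on use. With z_d the d-quantile of the standard normal and λ = φ(z_d)/(1 − d):

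- mean use rises by λ SD;
- the SD of use becomes s, where s² = 1 + z_d·λ − λ²;
- the correlation becomes r·s / √(1 − r² + r²s²).

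For d = 0.30: z_d = −0.524, λ = 0.497, s = 0.702. With r = 0.50 the result is 0.50 × 0.702 / √(0.75 + 0.25 × 0.702²) = 0.376. Simulation with one million pairs gave the correlations below and agrees with the formula.

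| Omitted | Analysed (per cohort) | SD of use | True r 0.50 becomes | True r 0.30 becomes |
|---|---|---|---|---|
| 10% | 54 (27) | 0.84 | 0.44 | 0.26 |
| 20% | 48 (24) | 0.76 | 0.40 | 0.23 |
| 30% | 42 (21) | 0.70 | 0.38 | 0.22 |
| 40% | 36 (18) | 0.65 | 0.35 | 0.20 |

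**Step 4: within-subject change.** Suppose that there is no true change and that change correlates ρ with use. The mean change among those kept is ρ × λ, in SD units of change. False-positive rates are from 10,000 simulated trials of 60 participants each, with a two-sided 5% paired test.

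| Omitted | Spurious change, ρ = 0.2 to 0.5 | False-positive rate, ρ = 0.2 to 0.5 |
|---|---|---|
| 20% | 0.07 to 0.18 SD | 8% to 24% |
| 30% | 0.10 to 0.25 SD | 10% to 38% |

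**Limits of the model.** A 14-day gap is not the same as the bottom share of total use. A heavy user who stops in week 6 would be omitted, while someone who uses the app sparsely but never leaves a 14-day gap would stay. The tables show the kind of distortion and its plausible order, not a prediction for this trial.

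**The case against.** The strongest reply is that the rule is narrower than it looks and will seldom apply. Much of this is fair, and it rules out several stronger readings.

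- **That stopping is lost altogether.** The text says further analysis, and the preceding sentence derives time of dropout from the logs. That can be done only for people who dropped out, so a description of use over time may well include them. The t tests and the PLS-SEM, which come after the rule, get no such relief.
- **That exclusion acts on one arm only.** A reader might infer this because cohort 2 has no app while it waits. However, cohort 2 meets the same rule once it has the app, and the only effect test named is within-subject. What remains is conditional: any comparison of cohort 1 with the waiting list would no longer be between the groups as randomised.
- **That skipping the diary leads to removal on the day the modules open.** The PACO App section says: "All other modules become available when the food diary has been completed for 7 days or automatically after 14 days". The trigger is no interaction at all, not an unfinished diary. There is a daily dialogue, a phone call within 2 working days, and contact after 7 inactive days. These contacts may make the rule fire less often; they do not change what it does when it fires.
- **That people who stop are no longer surveyed.** The Procedure section invites participants to T1 and T2 without excepting inactive ones. Asking why people stopped suggests that their answers are wanted, and the paragraph on qualitative analysis contains no exclusion.
- **That the study is explorative.** Participants does say so. But Research Questions still asks to what extent PACO reduces loneliness and improves eating behaviour, and the rule bears on that answer.

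**Conclusion.** The point stands for the effect tests and the CEU. As written, the plan selects participants on a post-randomisation primary outcome and truncates the variable that the CEU is meant to explain. This follows from the text and needs no assumption about rates.

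The size is illustrative only. If 10-40% are omitted from the low end of use, 54-36 participants remain and a true correlation of 0.50 falls to about 0.44-0.35. A reader might infer that the health effect is certain to be overstated. The document does not establish that: upward bias requires persistence and improvement to be positively correlated, which is plausible but nowhere stated.

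**What to change.** In Data Analysis, replace the omission with the following:

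- Analyse all randomised participants in their assigned cohort.
- State that T1 and T2 are sought from everyone, whatever their use. T2 matters most, because Table 1 shows usability, enjoyment, aesthetics, privacy concerns, control and perceived usefulness measured only then.
- Keep low or zero logged use as observed values in the use analyses and the CEU.
- Use the 14-day criterion only to describe dropout and to define a labelled sensitivity analysis.

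The cost is a change of analysis wording and a clear statement about follow-up. The downside is missing or weak data: some who stop will not answer T1 or T2, and people who barely used PACO may be able to rate it only poorly at T2. A likelihood-based or multiple-imputation method is therefore needed.
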